### Participants

We initially aimed to include a total of 900 participants from six countries (Netherlands, US, Japan, Israel, Germany, Switzerland), comprising 300 persons with (early) dementia, 300 family caregivers and 300 physicians. From each country, we planned to recruit 50 dyads of persons with dementia and their family caregivers, and 50 physicians. Recruitment procedures for persons with dementia, their family caregivers and physicians are adapted for each participating country in close collaboration with our local partners. We amended the participant target due to difficulty recruiting persons with dementia and family caregivers (see paragraph ‘Adjustments to protocol’).

We work with healthcare professionals, primarily physicians working in memory clinics and hospitals, to recruit dyads of a person with dementia and their family caregiver. We also recruit via general practitioners (GPs) and dementia case managers. When persons with dementia visit their physician, the physician will offer an information package to eligible participants. Participants can then: (a) directly contact the research team, or (b) inform their physician about their decision. The physician will then ask for permission to forward the contact information of the pair to the research team.

For the recruitment of the physicians, the study is announced via relevant webpages and newsletters of local professional networks and educational institutions. The researchers also directly contact physicians who are already in their professional network by email to inform them about the study. The researchers send physicians who are interested an information package about the study and call them to explain the study in more depth and to schedule an appointment for the assessment.

The inclusion criteria for the person with dementia are: (1) has a diagnosis of irreversible dementia established by a physician; (2) has been informed about and is aware of their diagnosis; (3) has a family caregiver who is willing to participate in the study; (4) has decision-making capacity and is able to communicate through sufficient memory and language; (5) is able to understand and sign the consent form; (6) has adequate vision and hearing (can be achieved by using corrective lenses and hearing aid if required); and (7) consents to participate.

There is no formal capacity test to avoid feelings of failure if that would result in denying participation. We rely on the clinician’s estimation of whether people have capacity to decide to participate in the study and are able to do so. If needed, we provide the referring clinicians with three relevant items of the Dementia Severity Rating Scale to aid clinical judgement of the capacity to give meaningful responses in the interview [56]. For the ‘Memory’ item a score of ≤ 2, ‘Speech and Language’ item a score of ≤ 3, and ‘Ability to make decisions’ item a score of ≤ 2 indicate sufficient ability for the purpose of this study. If the person with dementia is currently affected by a severe psychiatric disorder (e.g., major depression, schizophrenia, substance abuse, post-traumatic stress disorder) as diagnosed by a psychiatrist, psychologist, or physician, or if the participant is expected to die in a few weeks, they are excluded.

Family caregivers can participate if (1) they are willing and able to participate in the study; (2) the person with dementia they care for is willing and able to participate; (3) are ≥ 18 years old. Physicians can participate if they practice a specialty that includes provision of end-of-life care for persons with dementia. Depending on the country, the specialty could be primary care physicians such as GPs, elderly care physicians, geriatricians, geriatric psychiatrists, neurologists, and palliative care physicians.

### Study setting

The study setting differs for the person with dementia and their family caregiver versus physicians. Ideally, the assessment with the person with dementia and their family caregiver takes place at the local research site, at their home or the practice of their healthcare professional. This can be at a memory clinic, hospital, or their physician’s practice. The assessment with the physicians will take place at their office or online via videocall.

### Procedure

Participation in the study consists of a one-time assessment of 60 (physicians) to 90 min (person with dementia and family caregiver). During the assessment, the participants view four animation videos (range duration 1:53 to 4:51 min depending on the intervention and language). After each video, they are interviewed. The order of the two ACP-videos and the Technology video is randomized by an independent statistician. Due to the potential sensitivity of the topic, the Euthanasia video is shown last. The participants also complete a brief survey with items about attitudes concerning the end of life, views on dementia, decision-making, coping, and demographic information. Table 1 gives an overview of all the instruments and items in the survey. If needed, a translator is present during the assessment.

The in-person assessment with the person with dementia and their family caregiver is be conducted by two researchers or one researcher and a volunteer. Volunteers and translators are trained by the research team in advance. After finishing the assessment, the pair is debriefed and receives information about what to do if they feel distressed afterwards related to the assessment.

**Table 1 Tab1:** Overview of the instruments per group

Constructs	Items in the survey	Respondent group		
		Person with dementia	Family caregiver	Physician
Attitudes towards the end of life	• 4 items from the Death Anxiety Questionnaire (58)	X	X	X
	• one item of each of the five subscales from the Death Attitude Profile-Revised (DAP-R) (59, 60)	X	X	X
	• Item about general level of comfort with talking about the end of life (11)	X	X	X
Caregiver burden	Zarit Burden Interview, 6-item version (ZBI-6) (61–65)		X	
Concerns about future	Three items from the subscale ‘Preparation for end of life’ of the Quality of life at the end of life (QUAL-E) (68)	X		
Coping styles	Brief COPE subscales: Use of instrumental social support; Active coping; Denial; Use of emotional social support; Acceptance; Planning; Religious coping (69, 70)	X	X	X
Decision-making	• Is your relative capable of making decisions on medical treatments by themselves? (11)		X	
	• Does your relative’s faith or spiritual background influence decisions about care and treatment? (11, 71)		X	
	• Medical decision making (11)			X
Dementia	• Dementia diagnosis • Quick Dementia Rating System (QDSR) - cognitive subscale (72)	O O		
Demographic variables	Age, gender, educational level, country of birth, religious background, worked in healthcare, relation to person with dementia, living situation of person with dementia, work status family caregiver	O	X	X
Goals of care	• The most important goal of [your relative’s] health care is to preserve my [his/her] life as long as possible, even if that requires treatments that may cause pain or discomfort. (11)	X	X	
	• When you think about the goals of care for your relative, which of the following do you most strongly consider? what you think your relative would probably want for themselves, what you want for your relative, what you think the physician of your relative wants for themselves, and don’t know		X	
Illness cognition	Rating of the following statements:			
	• Dementia is a disease you can die from. (11, 37)	X	X	X
	• Dementia is a normal part of the ageing process. (73, 74)	X	X	X
	• Palliative care applies from the time of diagnosis to the stage of severe dementia. (75)			X
Illness perception	Brief Illness Perception Questionnaire (IPQ-B) - one item from the Consequence, Personal Control, Illness concern and Emotional representation dimensions (76–78)	X		
Interpersonal closeness	Inclusion of other in the self scale (IOS) (79)		X	
Locus of control	4-item version of the Locus of Control scale (IE-4) (80)	X	X	X
Mood	2-item Patient Health Questionnaire depression module (PHQ-2) (81)	X O	X	
Personal experiences with dementia	Have you personally experienced a family member or friend having advanced dementia at the end of their life? (82)	X	X	X
Preparedness	Item about preparedness for the end of life of relative (83)		X	
Work experience	Specialty, additional palliative training, work setting, years of experience with dementia care (82)			X

*Note*: X = fills in questions about themselves, O = questions about person with dementia filled in by family caregiver

### Sample size calculation

The number of participants is determined by the primary objective of the trial (acceptability). We will use logistic regression analyses and before the COVID-pandemic, we aimed at a total of 6 (countries) x 3 groups) x 50 = 900 respondents for sufficient power according to the 10 events per variable rule of thumb, for a minimum acceptability or non-acceptability rate of 10%. Therefore, with percentages of 10% and up, power would suffice to assess differences between 6 countries and 3 respondent groups. Testing of associations with other characteristics, i.e. life view and demographic and personality characteristics, is exploratory. Also see paragraph ‘Adjustments to protocol’.

### Adjustments to protocol

Due to COVID-19 hitting the world in the beginning of 2020, the start of the data collection was postponed to July 2020 and is extended till 2023.The COVID restrictions caused severe delays in the data collection. Healthcare providers were hesitant to join the study both as a participant and to assist in the recruitment of persons with dementia and their family caregivers due to the increased workload and wanting to protect their patients. Therefore, adjustments were made to the protocol. The recruitment strategies for persons with dementia and family caregivers were expanded to recruiting through dementia cafes and social media. In the US, an online service of patients who have volunteered to participate in research studies (Research Match) and electronic resources were used to identify additional persons with dementia. When identified from the electronic record, their physician was asked if it is acceptable to contact the patients and caregivers. A telephone screening script was developed to check whether the person with dementia and family caregiver met our inclusion criteria.

After completing the data collection of the Dutch and US physicians, and after interviewing 15 dyads of person with dementia and family caregiver in the Netherlands, we decided to reduce the number of interviews to 15 per country per group. This was because 50 dyads was no longer considered feasible within the remaining study time and because we found data saturation in the Dutch data was reached after 12–15 interviews [57]. For physicians, we decided to offer a full self-report online version of the assessment after 15 interviews, where they can view the animation videos themselves and then indicate whether they find each intervention acceptable. Open text fields are provided for an optional explanation of the answers. In general, this online option was not deemed feasible for the dyads (e.g., limitations in digital-literacy, availability of technology for online meeting, etc.), and not approved of by the Dutch ethics committee due to the potential sensitive topics. For the dyads, the focus will thus be on the qualitative data.

For the adjusted protocol a new power calculation was performed. We will use logistic regression analyses and expect that collecting physician data (n = 50) in a total of 6 (countries) results in 300 physician respondents. Power depends strongly on the type of intervention as this has varied, so far in data collected in the Netherlands, the US and Japan, from acceptable for almost all (advance care planning interventions) to acceptable for closely around half. According to the 10 events per variable rule of thumb, for 7 variables, with 300 respondents, 70 events suffice for acceptability in ratios close to half of respondents, but would not suffice for interventions that are (not) acceptable for the large majority of the respondents. However, examining associations with acceptability is less relevant for interventions which are endorsed or rejected by the great majority.

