### Hypotheses

For the acceptability of the interventions per group, we expect that the ACP intervention with detailed advance treatment orders will be most often acceptable and euthanasia least often acceptable in physicians. No hypotheses on acceptability rated by persons with dementia compared to the other groups are formulated because not enough is known about their views on this matter to formulate specific hypotheses. With regard to acceptability by country, we hypothesize that the ACP intervention with detailed advance treatment orders will be most often acceptable in countries where patients have high autonomy in decision making about medical procedures and care, and where people may feel they need a defence against medical overtreatment, while sanctity of life is not necessarily a dominant principle (in particular, the US). Technology for symptom monitoring when unable to self-report, such as use of cameras in the dying phase, is expected to be most often acceptable in technology-minded countries (Japan, Israel and US). Euthanasia may be most often acceptable in countries that have euthanasia or PAS regulation already in place for a while (in particular the Netherlands and Switzerland) and the least acceptable in countries where ending life is highly controversial (Germany, Israel and Japan).

For the explorative analyses, we expect demographics, variables indicating life view such as religion, view on dementia, attitudes regarding life-prolonging treatment and death and dying, and variables indicating personality such as coping strategy to be associated with acceptability of the interventions. These aspects of life view and personality are selected because they may relate to control. In explaining diversity in acceptability of ACP, individual differences may be more important than differences between countries and respondent groups (hypothesized based on a study in physicians in the UK and the Netherlands; [53]), with those tending to planning as a coping strategy more likely to find the interventions acceptable. Contrary, it could be that people with higher death anxiety are less likely to find the interventions acceptable, as it has been related to fewer preparations for death in people with advanced cancer [54, 55].

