### Primary study parameter(s)

The primary outcome is acceptability of the interventions, assessed during the interview. The two primary acceptability measures are: [1] whether the participant finds the intervention acceptable for dementia care, and [2] whether they want the intervention for themselves. This means, whether persons with dementia want it for themselves, family caregivers for their relative and whether physicians would use it at request. The primary outcome is a categorical variable with three categories (‘yes’, ‘no’ and ‘don’t know’ as a valid answering option).

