### Data analyses

Descriptive statistics will be used to present the acceptability of the four interventions. The internal consistency of the scales will be calculated using Cronbach’s alpha. Descriptive statistics will be calculated to describe the demographics of the respondent groups per country.

We will use logistic regression analyses with acceptability of the intervention as the dependent variable to examine differences in acceptability between group and countries. ‘*Do not know*’ as a response option is often ignored and excluded from the denominator. A dichotomous variable will be create with a denominator of ‘acceptable versus not acceptable plus do not know’. The analyses will be unadjusted and adjusted for the most important life view or personality parameter (religion for euthanasia, planning for the other interventions). We will explore associations between acceptability and participant characteristics (gender, educational level, age, severity of cognitive impairment for persons with dementia, and palliative care training for physicians) and personality (locus of control, coping), depression, medical decision making, professional or personal experience with dementia, physician’s comfort with end-of-life conversations, and caregiver burden, and life view (religion, death anxiety/attitude, preparedness for end of life, priority quality vs. quantity of life, illness cognition). For this, we will use stepwise backward regression analyses. The analyses will be done with and without adjustment for country and group (forced in the stepwise regression analyses).

Qualitative data from the interviews will be used to map possible ambiguity regarding being in control through the interventions, and as to why and in what situation the participant feels the interventions are acceptable. A content analysis regarding acceptability of the interventions will be conducted. Additionally, across all interviews, we will conduct a thematic analysis on perceptions of control. Data collection and data analysis will be executed iteratively. Coding is supported by the software program ATLAS.ti.

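### Among physicians, interview versus online self-report is partly confounded with country, and the country regression has no mode term

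*Protocol article*

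**What the plan says.** Under Study setting, physician assessments are led by a researcher: "The assessment with the physicians will take place at their office or online via videocall". Under Primary study parameter(s), the outcome is tied to that mode: "The primary outcome is acceptability of the interventions, assessed during the interview".

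Adjustments to protocol then dates a change. It begins "After completing the data collection of the Dutch and US physicians" (the 15 Dutch dyads had also been interviewed by then) and continues "we decided to reduce the number of interviews to 15 per country per group". For physicians it adds: "For physicians, we decided to offer a full self-report online version of the assessment after 15 interviews". The article describes that version as one "where they can view the animation videos themselves and then indicate whether they find each intervention acceptable". This is not the videocall of Study setting, because no interviewer takes part.

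Data analyses compares groups and countries by logistic regression, counting don't-know answers with non-acceptance. On adjustment it says: "The analyses will be unadjusted and adjusted for the most important life view or personality parameter", meaning religion in the euthanasia model and planning in the other three. The exploratory covariates are listed, and the terms forced into the stepwise models are country and group. Assessment mode appears in none of these places.

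The Discussion treats online assessment of physicians as a practical gain. The only related limitation it names is that time trends cannot be adjusted for.

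**The concern.** If the later countries answer largely by self-report and the Netherlands and US answered an interviewer, part of any Dutch or US difference from the others may be a difference in mode. The protocol itself regards euthanasia as sensitive, since it shows that video last. Any effect of mode on the use of the don't-know option would also enter the dependent variable directly.

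The exposed contrasts include stated hypotheses. The US is singled out for detailed advance care planning (ACP). Euthanasia is expected to be most acceptable in countries with established regulation, "in particular the Netherlands and Switzerland", and least acceptable in Germany, Israel and Japan. Since dyads are now mainly a qualitative sample and the revised power statement covers only the 300 physicians, the physician regression carries most of the quantitative country comparison.

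**Working it through.** **The plan's own figures.** 6 countries × 50 physicians = 300, and 10 events × 7 variables = 70 events. Both reproduce.

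**Inputs**
- From Adjustments to protocol: 50 physicians per country, self-report offered after 15 interviews, and Dutch and US physicians complete before the decision.
- Inferred from that order, not stated outright: the Netherlands and US have 50 interviews and no self-reports each.
- Assumed maximum in each of the other four countries: 15 interviews and 35 self-reports, a share of 35/50 = 0.70. Overall that is 4 × 35 = 140 of 300 (47%).
- Assumed mode effect d, the shift in acceptability under self-report: 5 to 20 percentage points, in either direction. The documents give no figure.

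**Bias** = d × difference in self-report share (signs dropped)

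| Contrast | Difference in share | Bias | d = 5 to 20 points |
|---|---|---|---|
| Netherlands or US vs one later country | 0.70 − 0 | 0.70d | 3.5 to 14 |
| US vs the other five | (0 + 4 × 0.70)/5 − 0 | 0.56d | 2.8 to 11.2 |
| Euthanasia: Netherlands + Switzerland vs Germany + Israel + Japan | 0.70 − (0 + 0.70)/2 | 0.35d | 1.75 to 7 |
| Technology: Japan + Israel + US vs the other three | 1.40/3 − 1.40/3 | 0 | 0 |
| Netherlands vs US | 0 − 0 | 0 | 0 |

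**Can mode be separated from country?** Yes, because it varies within four countries.
- Within-country sum of squares of mode: 4 × 50 × 0.3 × 0.7 = 42.
- Total sum of squares: 300 × 0.4667 × 0.5333 = 74.7.
- R² of mode on country: 1 − 42/74.7 = 0.44. Variance inflation factor: 1/(1 − 0.4375) = 1.78.

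**Cost of adjusting** (linear approximation, residual variance s², variance of the mode coefficient s²/42)
- Netherlands vs Germany: unadjusted variance 2/50 = 0.04, added 0.70²/42 = 0.0117. The ratio is 1.29, so the SE rises about 14%. On the logistic scale at 50% acceptability, the SE of the log odds ratio goes from 0.40 to 0.45. For US vs Netherlands it stays at 0.40.
- Euthanasia block: unadjusted variance (2/4 + 3/9)/50 = 0.0167, added 0.35²/42 = 0.0029. The ratio is 1.175, so the SE rises about 8%.
- Interview-only, Netherlands vs Germany: √[(1/50 + 1/15)/0.04] = 1.47, so the SE rises 47%.
- Events: one more term makes eight variables, so 10 × 8 = 80 events (26.7% of 300) instead of 70 (23.3%).

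**The case against.** The strongest reply concerns size and reach, and much of it stands.

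- **The mode effect is unsourced.** Both modes use the same standardised videos and ask physicians about acceptability, and nothing in the documents shows that answers differ. A reader might infer that the country comparison is biased. The documents support only that it could be, and that the model as written cannot tell.
- **The 70% is a ceiling.** Self-report is offered, not imposed, and uptake is not given. Some Japanese data existed when power was recalculated, so Japan's interview share may exceed 15/50.
- **Reach is limited.** A reader might infer that mode and country cannot be separated, or that every country hypothesis is affected. Neither follows. The confounding is partial, and the technology block and Netherlands versus US balance out. For ACP, the article reports near-universal acceptance in the data so far, which leaves little room for a shift and makes the US figure of 0.56d of small practical weight. Country differences are also a secondary objective.
- **The mode coefficient is not clean.** Interviews come first and self-report follows by choice, so the coefficient also carries calendar time and self-selection. That argues against making it the sole adjustment in every model.
- **The article is condensed, and the Discussion already concedes sequential data collection.** A sensitivity analysis could sit in a fuller plan. But the article does spell out the model's adjustments and forced terms, describes the mode change, and still defines the outcome as measured by interview. The time-trend caveat does not tell a reader that the method of measurement differs by country.

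**Conclusion.** The point holds in this form: as written, the plan leaves assessment mode partly confounded with country among physicians, and neither the model nor the stated limitations take account of it. At the maximum split, the bias is 0.70d for the Netherlands or US against a single later country and 0.35d for the euthanasia block contrast.

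This rests on three assumptions: all Dutch and US physicians were interviewed, every slot after the first 15 elsewhere is self-report, and mode has a common effect d across countries. Lower uptake shrinks the bias in proportion, and d = 0 removes it. The practical exposure is mainly euthanasia and pairwise contrasts of the Netherlands or US with a later country.

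This should be fixed. A reader might take it as fatal to the country comparison. The documents do not support that, because d is unknown, the split is an upper bound, and mode can be estimated within the four mixed countries.

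**What to change.** 1. Record for every physician whether the assessment was an interview (in person or by videocall) or online self-report.
2. Report the physician country models with and without a mode covariate, and show the within-country mode effect from the mixed countries. Fix this before the analysis.
3. Add an interview-only sensitivity analysis.
4. Correct Primary study parameter(s) so that it covers self-reported acceptability.
5. State in the Discussion that Dutch and US contrasts with the other countries are partly confounded with mode, and that the mode term assumes a common effect and is mixed with calendar time and choice of mode.

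The cost is one data field, one covariate and one extra table. Precision falls by the amounts worked out above (SE up about 14% for Netherlands versus Germany and about 8% for the euthanasia block), and the events requirement rises to 80. That is still met where acceptability is near half. The interview-only analysis is much less precise, so it serves as a check and should not replace the main result.

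### The revised sample-size justification is called a power calculation, but it is an events-per-variable count and shows no power for the planned country and group comparisons

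*Protocol article*

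**What the plan says.** The Sample size calculation section of the Protocol article ties the number of participants to the primary objective: "The number of participants is determined by the primary objective of the trial (acceptability". For the pre-pandemic target of 900 it applies the 10-events-per-variable rule at a minimum rate of 10% and concludes that "with percentages of 10% and up, power would suffice to assess differences between 6 countries and 3 respondent groups".

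The Adjustments to protocol section cuts dyads to 15 per country and says of the reduced design: "For the adjusted protocol a new power calculation was performed". The inputs are that "collecting physician data (n = 50) in a total of 6 (countries) results in 300 physician respondents" and that acceptability so far has ranged "from acceptable for almost all (advance care planning interventions) to acceptable for closely around half". The result, under the same 10-events-per-variable rule, is: "for 7 variables, with 300 respondents, 70 events suffice for acceptability in ratios close to half of respondents". The section adds that the count would fall short for interventions that most respondents accept or reject.

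Under Objectives, description of acceptability is primary and differences between groups and countries are secondary. Hypotheses names countries expected to be higher or lower. Data analyses keeps logistic regression "to examine differences in acceptability between group and countries".

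**The concern.** An events-per-variable rule limits the number of parameters relative to the number of outcome events, so that coefficients are reasonably stable. It says nothing about the chance of detecting a given difference. That requires a significance level, a difference and the sizes of the groups compared, and the article gives none of these for the comparisons. Both the old and the revised justification therefore speak of power on a basis that cannot yield it.

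At stake is how the country and group results are read. If the design is thought to be adequately powered, a non-significant difference between two countries' physicians may be taken as evidence of similarity when a sizeable gap could have been missed. The sizing also covers physicians only, while the planned models still include respondent group.

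**Working it through.** **Inputs from the article.** 50 physicians in each of 6 countries = 300. After the reduction, 15 persons with dementia and 15 caregivers per country, so 6 × 15 = 90 of each. Seven variables, 10 events per variable. Acceptability between about one half and almost all.

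**Assumptions, because the article states none.** Two-sided 5% test, 80% as reference power, and 50% versus 70% as the example difference, with 50% taken from the article's own description of the lower end of the range.

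**1. The plan's figure.** 10 × 7 = 70 events, which reproduces. As a share of physicians, 70/300 = 23.3%. Counting the rarer outcome as the event, the rule is met for any acceptability from 23.3% to 76.7%. At 50% there are 150 events, or 150/7 = 21.4 per variable. No step uses a significance level or an effect size.

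**2. Power for two countries' physicians (50 versus 50).** Normal approximation, pooled variance under the null:

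power = Φ[(|p1 − p2| − 1.96 × SE0) / SE1]

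where SE0 = √[p̄(1 − p̄)(1/n1 + 1/n2)] and SE1 = √[p1(1 − p1)/n1 + p2(1 − p2)/n2].

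For 50% versus 70%: p̄ = 0.60, SE0 = √(0.24 × 0.04) = 0.0980, SE1 = √(0.25/50 + 0.21/50) = 0.0959. Then (0.20 − 0.1920)/0.0959 = 0.083 and Φ(0.083) = 0.533.

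Other methods for the same pair: unpooled variance 55.0%, arcsine 53.9%, exact chi-square 54.6%, Fisher 46.3%. For 40% versus 60% the formula gives 51.6%.

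**3. Detectable difference, 50 versus 50, from a 50% base.** At 50% versus 77%: SE0 = 0.0963, SE1 = 0.0924, (0.27 − 0.1887)/0.0924 = 0.88, power 81%. So 80% power needs about 27 points. Reaching 80% for 50% versus 70% would take 93 physicians per country.

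**4. Where power is better.** Same formula:

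| Contrast (physicians) | Rates | Power |
|---|---|---|
| 50 v 50 | 70% v 90% | 71% |
| One country v other five (50 v 250) | 70% v 50% | 75% |
| Two countries v three (100 v 150) | 50% v 70% | 89% |
| Three countries v three (150 v 150) | 50% v 70% | 95% |

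**5. All physicians versus all caregivers (300 versus 90).** At 50% versus 66.6%: SE0 = 0.0599, SE1 = 0.0575, (0.166 − 0.1174)/0.0575 = 0.845, power 80%. The detectable difference is about 17 points.

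**6. Precision for the descriptive primary objective.** 95% half-width at 50% = 1.96 × √(0.25/n): 13.9 points for n = 50 and 25.3 points for n = 15.

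**The case against.** Much of the defence stands.

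- **No arithmetic error.** A reader might infer that the count was miscalculated or misread. It was not: 70 events is right, the article does not say the rule is met only near one half, and it is right that a large majority either way leaves too few events. The range of 23% to 77% is more precise but corrects nothing false.
- **Origin of the seven variables.** A reader might infer that they are five country and two group indicators left over from the three-group design. The article does not list them, and a physician-only model with adjustment terms could also have seven. The inference cannot be supported.
- **Only very large gaps detectable.** A reader might conclude this from the 53%. It rests on an assumed 20-point gap, an assumed 5% level and a pairwise contrast near one half. Most of the country hypotheses concern sets of countries, for which pooled contrasts have 89% to 95% power at the same rates. The article plans neither a correction over all country pairs nor a group comparison within a country, so figures for those would have no target.
- **Superseded text.** The statement that power would suffice belongs to the 900-person design, and the adjusted section does not repeat it.
- **Dyads.** The article moves their focus to qualitative data, justifies 15 by saturation, and states no hypothesis comparing persons with dementia with the other groups.
- **Condensed article.** Precision figures may stand in the full protocol, so their absence is not itself the point.

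None of this turns an event count into power. The adjusted section still uses that name, and Data analyses still includes group in the models without saying that the dyad comparisons are now only descriptive.

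**Conclusion.** The point holds as one of labelling and unsupported inference. The adjusted design is described as having had a power calculation when only a model-size check was done, and the older claim of sufficient power rested on the same rule.

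Under the stated assumptions, power between two countries' physicians is about 53% for 50% versus 70%, and 80% is reached only at about 27 points. Power is materially better near the extremes and for pooled sets of countries, so the design is not weak for every hypothesis. The pooled figures apply at 50% versus 70%; they do not describe the advance care planning interventions, which the article says almost all respondents so far accept.

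Severity is moderate: country and group differences are a secondary objective, the primary one is descriptive, and the article concedes the limit for near-unanimous interventions.

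**What to change.** 1. In Adjustments to protocol, call the events-per-variable count a model-size check, say that with seven parameters it is met for acceptability of about 23% to 77%, and name the seven parameters.
2. Make clear that the claim of sufficient power in Sample size calculation does not carry over to the adjusted design.
3. Give the precision that serves the descriptive primary objective: 95% half-widths at 50% acceptability of about 14 points for 50 physicians and about 25 points for 15 persons with dementia or 15 caregivers.
4. Give detectable differences at 80% power for the planned contrasts, with significance level and base rate stated: about 27 points between two countries' physicians and about 17 points for 300 physicians versus 90 caregivers, both from 50%. Where a hypothesis concerns a set of countries, give the figure for that pooled contrast.
5. In Data analyses, present comparisons involving the dyads as descriptive estimates with confidence intervals, in line with the qualitative focus already adopted for them.

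The cost is text only. No participants are added; the stated properties become less favourable for pairwise country comparisons.
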